### Study design

The protocol stated that patients were to be screened for eligibility for the study 21±7 days prior to randomization. Eligible patients were to undergo a 2-week, open-label, placebo run-in period prior to randomization, during which metformin IR was to be continued at the patient’s usual dose. Following the run-in period, patients still meeting the inclusion criteria were randomized 1:1 to receive empagliflozin 25 mg qd or glimepiride 1–4 mg qd in a double-blind, double-dummy manner for 2 years, in addition to metformin IR (Figure 1). Glimepiride was initiated at a dose of 1 mg/day, with the recommendation for uptitration if fasting plasma glucose (FPG) (assessed by home monitoring) was >110 mg/dL to 2 mg/day at week 4, to 3 mg/day at week 8, and to a maximum of 4 mg/day at week 12. Uptitration was to be withheld if it would place the patient at risk of hypoglycemia and should not take place after week 12. The glimepiride dose can be downtitrated at any time to prevent recurrent hypoglycemia. Randomization was achieved using a computer-generated random sequence communicated via a third-party interactive voice or web response system. Randomization was stratified by HbA_1c_ at screening (<8.5% and ≥8.5%), eGFR according to the Modified Diet Renal Disease (MDRD) formula (<90 mL/min/1.73 m^2^ and ≥90 mL/min/1.73 m^2^) and region (Europe/South Africa, Asia, North America, and Latin America). Patients who participate in the 2-year randomized treatment period are eligible to participate in a 2-year extension period, during which they will continue to receive the treatment allocated at randomization in a double-blind, double-dummy manner. All patients will be followed up for 4 weeks after the last dose of study drug.

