The efficacy analyses will be performed on the full analysis set (FAS), i.e. all randomized patients who received ≥1 dose of study drug and had a baseline HbA_1c_ assessment, using the last observation carried forward (LOCF) methodology for imputation of missing data. Efficacy data after the first intake of rescue medication will be set to missing. For the primary endpoint, an analysis of covariance (ANCOVA) model will be used with randomized treatment, eGFR and geographical region as fixed effects and baseline HbA_1c_ as a covariate. Sensitivity analyses of the primary endpoint will be undertaken in the per-protocol set (PPS104: patients in the FAS without any important protocol violations during the first 104 weeks’ treatment, such as violating the inclusion or exclusion criteria, changing dose of background metformin IR, taking the incorrect trial medication, or compliance <80%), FAS104 completers (patients in the FAS who complete the 2-year treatment period and have HbA_1c_ values for the end of the treatment period) and PPS104 completers (FAS104 completers who do not have any important protocol violations) using the same model and the LOCF approach to missing data. Additional sensitivity analyses include a restricted maximum likelihood-based model repeated measures (MMRM) approach in observed cases in the FAS to determine the effect of empagliflozin on HbA_1c_ over time. Secondary endpoints will be analyzed using the same model as the primary endpoint, with the continuous baseline values of the endpoint being investigated included as an additional covariate. Blood pressure data after changes in antihypertensive medication will be set to missing and imputed using LOCF.

All safety endpoints will be analyzed in the treated set, i.e. all patients who received ≥1 dose of study drug and presented using descriptive statistics. Confirmed hypoglycemic events will be analyzed using Cochran-Mantel Haenszel tests stratified by baseline HbA_1c_ (<8.5% vs. ≥8.5%). Change from baseline in lipid parameters will be analyzed using ANCOVA. Time-to-event analyses (Kaplan-Meier) for onset of new microalbuminuria (albumin/creatinine ratio [ACR] ≥30 mg/g), onset of new macroalbuminuria (ACR ≥300 mg/g), and progression from microalbuminuria to macroalbuminuria groups compared using log-rank tests.

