## Results

Between August 2010 and June 2011, 1549 patients across 173 sites in 23 countries were randomized to receive study drug, of whom 1545 were treated. The baseline characteristics of the treated patients are shown in Table 4. The mean (SD) age was 55.9 (10.4) years, the mean (SD) HbA_1c,_ was 7.92 (0.84)% and the mean (SD) BMI was 30.11 (5.29) kg/m^2^. Mean (SD) systolic blood pressure was 133.5 (15.9) mmHg and mean (SD) diastolic blood pressure was 79.5 (9.4) mmHg, with 68.5% of patients having uncontrolled hypertension (≥130/80 mmHg).

**Table 4 T4:** Baseline characteristics (treated set: n=1545)

Gender, n (%)	
Male	854 (55.3)
Race, n (%)	
Caucasian	1017 (65.8)
Asian	507 (32.8)
Black/African-American	20 (1.3)
Hawaiian/Pacific Islander	1 (0.1)
Ethnicity, n (%)	
Non-Hispanic/Latino	1233 (79.8)
Hispanic/Latino	312 (20.2)
Region, n (%)	
Europe/South Africa	639 (41.4)
Asia	434 (28.1)
Latin America	276 (17.9)
North America	196 (12.7)
Age (years), mean (SD)	55.9 (10.4)
Time (years) since diagnosis of T2DM, n (%)	
≤1	172 (11.1)
>1 to 5	677 (43.8)
>5 to 10	425 (27.5)
>10	271 (17.5)
Body weight (kg), mean (SD)	82.8 (19.2)
Body mass index (kg/m^2^), mean (SD)	30.1 (5.3)
Body mass index (kg/m^2^), n (%)	
<25	243 (15.7)
25 to <30	587 (38.0)
30 to <35	434 (28.1)
≥35	281 (18.2)
Waist circumference (cm), mean (SD)	
Male	104.1 (13.0)
Female	98.8 (12.8)
HbA_1c_ (%), mean (SD)	7.9 (0.8)
HbA_1c_ (%), n (%)	
<8.5	1173 (75.9)
≥8.5	372 (24.1)
Fasting plasma glucose (mg/dL), mean (SD)	149.9 (33.9)^a^
HOMA-IR (mU/L x mmol/L), mean (SD)	6.03 (5.31)^b^
HOMA-B (mU/mmol), mean (SD)	77.0 (79.0)^c^
Cardiovascular medications, n (%)	1174 (76.0)
Antihypertensive agents	933 (60.4)
Lipid lowering agents	805 (52.1)
Acetylsalicylic acid	498 (32.2)
Systolic blood pressure (mmHg), mean (SD)	133.5 (15.9)
Diastolic blood pressure (mmHg), mean (SD)	79.5 (9.4)
Blood pressure controlled (<130/80 mmHg), n (%)	
Yes	486 (31.5)
No	1059 (68.5)
Serum lipids (mmol/L), mean (SD)	
Total cholesterol^d^	4.49 (1.01)
HDL-cholesterol^e^	1.25 (0.31)
LDL-cholesterol^f^	2.42 (0.86)
Triglycerides^e^	1.86 (1.29)
Markers of renal function and damage	
eGFR (mL/min/1.73 m^2^) according to MDRD, mean (SD)	88.0 (17.3)
eGFR (mL/min/1.73 m^2^) according to MDRD, n (%)	
≥90 (normal renal function)	633 (41.0)
60 to <90 (mild renal impairment)	877 (56.8)
30 to <60 (moderate renal impairment)	35 (2.3)
Urine albumin/creatinine ratio (mg/g), mean (SD)	40.22 (135.59)
Urine albumin/creatinine ratio (mg/g), n (%)	

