Identification of chronic kidney disease and its progression is based on the assessment of renal function (eGFR) and markers such as albuminuria [47]. Recommendations for intensive glycemic control for prevention or delay of diabetic nephropathy are based almost exclusively on studies that have demonstrated an improvement in albuminuria [47]. In patients with T2DM and chronic kidney disease, glycemic control is recommended to be part of a multifactorial intervention strategy that includes blood pressure control [47]. Thus, empagliflozin, which lowers blood pressure and body weight as well as improving glycemic control, may offer an advantage over glimepiride in reducing the onset or deterioration of albuminuria as a surrogate marker of glomerular and tubular damage. A limitation of this study is that as the incidence of doubling of serum creatinine, end-stage renal disease or death from renal disease is expected to be low in these patients with normal renal function or mild renal impairment at baseline, this study is not powered to detect differences in hard renal outcome events.

Reduction of macrovascular complications is an important goal in the management of patients with T2DM. While this study is not powered to detect a difference in CV outcomes - assuming a yearly rate of 4-MACE (major adverse cardiac events) (CV death, non-fatal myocardial infarction, non-fatal stroke, hospitalization for unstable angina) of 1% in this low-risk population, one might expect approximately 60 adjudicated 4-MACE in a 4-year trial - exploratory comparative effectiveness data could support treatment decisions until hard evidence emerges from dedicated CV outcome trials.

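### The albuminuria log-rank tests leave baseline ACR within the at-risk category unused, which costs efficiency, mainly for new microalbuminuria

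*Protocol article*

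**What the plan says.** The protocol article, Methods, Statistical analysis, plans "Time-to-event analyses (Kaplan-Meier) for onset of new microalbuminuria (albumin/creatinine ratio [ACR] ≥30 mg/g), onset of new macroalbuminuria (ACR ≥300 mg/g" and a third comparison, "progression from microalbuminuria to macroalbuminuria groups compared using log-rank tests". No stratification factor or covariate is named for any of the three.

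The same section names adjustment for other endpoints. The primary model has baseline HbA1c as a covariate. Secondary endpoints use the same model "with the continuous baseline values of the endpoint being investigated included as an additional covariate". For hypoglycemia: "Confirmed hypoglycemic events will be analyzed using Cochran-Mantel Haenszel tests stratified by baseline HbA_1c_ (<8.5% vs. ≥8.5".

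ACR does not enter the allocation either. Under Study design: "Randomization was stratified by HbA_1c_ at screening (<8.5% and ≥8.5%), eGFR according to the Modified Diet Renal Disease (MDRD) formula", with region as the third factor.

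Table 4 classifies baseline ACR as <30 mg/g in 1221 patients, 30 to <300 in 289 and ≥300 in 35. It also gives "Urine albumin/creatinine ratio (mg/g), mean (SD) 40.22 (135.59".

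New-onset albuminuria is listed among the safety endpoints and is not in the Table 3 hierarchy. The Discussion says that empagliflozin "may offer an advantage over glimepiride in reducing the onset or deterioration of albuminuria as a surrogate marker of glomerular and tubular damage", and that the study is not powered for hard renal outcomes. For the albuminuria events the article states no event rate, effect size, power or ACR measurement schedule.

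**The concern.** A patient who starts at 25 mg/g is much closer to the 30 mg/g threshold than one who starts at 3 mg/g. When risk differs this much within the risk set, high-risk patients have their events and leave early, the marginal hazard ratio moves towards 1, and an unstratified log-rank test loses power against one that compares like with like. The baseline value was classified for every treated patient (1221 + 289 + 35 = 1545), so using it needs no new data.

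Markers of renal function and damage belong to the trial's fourth stated objective. Safety endpoints are otherwise presented descriptively, so these log-rank tests are the only inferential comparisons stated for the albuminuria advantage that the Discussion raises. At stake is a greater chance of missing a real difference in albuminuria onset.

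**Working it through.** **1. The plan's own power figure.** There is none for albuminuria. The only one is for the primary endpoint: n per arm = 2·1.2²·(2.2414 + 1.6449)² / (0.30 − 0.05)² = 2.88 × 15.10 / 0.0625 ≈ 696, against 698 stated; power at 698 is 95.1%. That figure reproduces but says nothing about the albuminuria tests, so their power has to be simulated.

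**2. Baseline ACR.** A lognormal was fitted to Table 4: P(<30) = 1221/1545 = 0.790 and P(<300) = 1510/1545 = 0.977. This gives log-mean 1.845 and log-SD 1.928. The implied mean is exp(1.845 + 1.928²/2) = 40.6 mg/g, against 40.22 stated. The overall mean agrees, but Table 4 has no cut below 30 mg/g, so the shape there is extrapolated.

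**3. New microalbuminuria, threshold-crossing simulation.** The event is the first visit with ACR ≥30 mg/g, or two consecutive such values (confirmed). The plain log-rank is compared with a log-rank stratified by six baseline bands (<5, 5–<10, 10–<15, 15–<20, 20–<25, 25–<30 mg/g); two-sided 5%, 2000 runs per scenario. Assumptions not in the article: ACR reduction of 15% or 20%; within-patient log-SD 0.4 or 0.7; drift 5% per year; random-walk SD 0.35 per root-year; dropout 8% per year; ACR at weeks 12, 28, 52, 78 and 104, then six-monthly. Rejection rates in %, plain / stratified:

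| Weeks | Log-SD | No effect | 15% reduction | 20% reduction | 20%, confirmed |
|---|---|---|---|---|---|
| 104 | 0.4 | 4.3 / 4.9 | 36.6 / 55.5 | 58.4 / 81.8 | 49.7 / 60.4 |
| 104 | 0.7 | 4.4 / 5.3 | 31.1 / 44.5 | 52.2 / 69.0 | 39.4 / 46.0 |
| 208 | 0.4 | 4.4 / 4.6 | 36.5 / 61.8 | 59.1 / 85.2 | 53.9 / 69.6 |
| 208 | 0.7 | 5.1 / 5.8 | 31.9 / 48.2 | 54.5 / 74.7 | 46.9 / 54.7 |

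Single-value gains run from 44.5 − 31.1 = 13.4 to 85.2 − 59.1 = 26.1 points. Confirmed gains in the table run from 46.0 − 39.4 = 6.6 to 69.6 − 53.9 = 15.7. A repeat with separate code under the same assumptions (600 runs per scenario) gave 5 to 16 points for confirmed events, hence about 5 to 26 overall.

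**4. New microalbuminuria, other event models.** Here the hazard is proportional to ACR^β, with 4 years of follow-up, 5% yearly dropout, 1221 at risk and conditional HR 0.7. Power in %, plain log-rank to Cox with log baseline ACR, by assumed 4-year control incidence:

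| β | 15% | 25% | 35% | Gain (points) |
|---|---|---|---|---|
| 0.5 | 54.7 to 54.8 | 75.5 to 76.2 | 89.1 to 89.8 | 0 to 1 |
| 1.0 | 51.3 to 54.2 | 69.0 to 76.1 | 79.8 to 88.8 | 3 to 9 |
| 1.5 | 44.4 to 54.6 | 56.4 to 75.1 | 63.7 to 89.4 | 10 to 26 |
| 2.0 | 38.1 to 52.3 | 43.3 to 75.2 | 43.7 to 86.3 | 14 to 43 |

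At HR 0.8 and 15% incidence the gain is 0 to 8 points, while the marginal HR moves from 0.80 (β 0.5) to 0.85 (β 2). A differently built threshold-crossing model gave 1 to 42 points.

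The Schoenfeld formula shows why attenuation matters. Power = Φ(√(D/4)·|ln HR| − 1.96), with D the number of events. For D = 142 and HR 0.70 this is Φ(5.958 × 0.357 − 1.96) = 56.6%. For D = 144 and HR 0.74 it is Φ(6 × 0.301 − 1.96) = 43.9%.

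**5. The other two endpoints.** Under proportional hazards, onset of macroalbuminuria from ACR <300 changes by about −2 to +18 points with Cox and −1 to +8 with quartile strata. Progression (289 at risk, about 30 to 70 events) changes by about −3 to +21; at 15% incidence and HR 0.7 it is near zero (β = 1: 18.3% plain, 18.1% stratified, 17.0% Cox). Threshold-crossing runs for progression spread further with Cox, from −1 to +31 points. In exploratory runs with only about 10 to 17 macroalbuminuria events, adjustment gave a small loss.

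**6. Type I error.** In the models of step 4 under no effect, the plain log-rank rejected 3.8 to 5.8%, the quartile-stratified test 4.1 to 6.0% and Cox 2.7 to 4.5%. The gains are not bought with false positives.

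**The case against.** The strongest case is that nothing here is an error. The log-rank test is valid under randomization, and chance imbalance in baseline ACR is already covered by its error rate. The endpoint is a safety endpoint outside the hierarchy, so it need not be handled like HbA1c or body weight. The article is condensed, and strata or a supporting Cox model may be in the analysis plan. The size of the gain rests on invented inputs; the fitted lognormal puts about 35% of the at-risk group below 2 mg/g, which no figure in the article supports.

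All of that stands as a limit on the claim. It does not remove the point: the article does name the test, and the same section names a stratifier or baseline covariate for other endpoints, so a plain test is the natural reading.

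A reader might infer several stronger things that the document does not support:

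- **That the plan disregards baseline ACR altogether.** New onset and progression already define the risk sets by baseline category; only variation within the category is unused.
- **That the plan loses 5 to 26 points on all the albuminuria analyses.** That range is for new microalbuminuria under one set of assumptions.
- **That the treatment effect will be understated in a biased sense.** Marginal and conditional hazard ratios are different quantities, and a log-rank test estimates neither.
- **That patients near 30 mg/g are almost certain to have an event.** In the simulated controls, about 70 to 78% of those above 22 mg/g had one, against 0.2 to 6% of those below 5 mg/g (single-value definition). Both follow from the model.

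**Conclusion.** The point holds as an efficiency weakness. As stated, the three tests leave the starting value of the event variable unused within each risk set. Neither the validity of the tests nor the primary result is affected.

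For new microalbuminuria the direction of the loss is consistent across the models. Its size is not a property of the plan, because it depends on event rate, treatment effect, within-patient ACR variability, the ACR distribution below 30 mg/g and the visit schedule, none of which the article gives. It is negligible if baseline ACR is only weakly prognostic within the category and large if it is strongly so. For new macroalbuminuria and for progression no dependable gain can be claimed.

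This is a cheap improvement for an exploratory safety comparison.

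**What to change.** Change the albuminuria sentence in Statistical analysis before unblinding:

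- **New microalbuminuria:** a log-rank test stratified by pre-specified baseline ACR bands, for example the six in step 3, or a Cox model with log baseline ACR reporting the hazard ratio and 95% CI. Fix in advance which of the two is the main comparison. Keep the Kaplan-Meier curves, and keep the plain log-rank as a sensitivity analysis.
- **New macroalbuminuria:** stratify only by normo- versus microalbuminuria at baseline, and only if both groups (1221 + 289 = 1510) are in the risk set. The article does not say explicitly that they are.
- **Micro-to-macro progression:** at most two or three coarse bands within 30 to <300 mg/g, or leave the test plain.

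If the analysis plan already contains this, the article's sentence needs only to be read with it. The cost is a few lines of analysis-plan text, with no new data, visits or patients. The small downside is that the hazard ratio becomes conditional on baseline ACR and should be reported as such.

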## Results

Between August 2010 and June 2011, 1549 patients across 173 sites in 23 countries were randomized to receive study drug, of whom 1545 were treated. The baseline characteristics of the treated patients are shown in Table 4. The mean (SD) age was 55.9 (10.4) years, the mean (SD) HbA_1c,_ was 7.92 (0.84)% and the mean (SD) BMI was 30.11 (5.29) kg/m^2^. Mean (SD) systolic blood pressure was 133.5 (15.9) mmHg and mean (SD) diastolic blood pressure was 79.5 (9.4) mmHg, with 68.5% of patients having uncontrolled hypertension (≥130/80 mmHg).

**Table 4 T4:** Baseline characteristics (treated set: n=1545)

Gender, n (%)	
Male	854 (55.3)
Race, n (%)	
Caucasian	1017 (65.8)
Asian	507 (32.8)
Black/African-American	20 (1.3)
Hawaiian/Pacific Islander	1 (0.1)
Ethnicity, n (%)	
Non-Hispanic/Latino	1233 (79.8)
Hispanic/Latino	312 (20.2)
Region, n (%)	
Europe/South Africa	639 (41.4)
Asia	434 (28.1)
Latin America	276 (17.9)
North America	196 (12.7)
Age (years), mean (SD)	55.9 (10.4)
Time (years) since diagnosis of T2DM, n (%)	
≤1	172 (11.1)
>1 to 5	677 (43.8)
>5 to 10	425 (27.5)
>10	271 (17.5)
Body weight (kg), mean (SD)	82.8 (19.2)
Body mass index (kg/m^2^), mean (SD)	30.1 (5.3)
Body mass index (kg/m^2^), n (%)	
<25	243 (15.7)
25 to <30	587 (38.0)
30 to <35	434 (28.1)
≥35	281 (18.2)
Waist circumference (cm), mean (SD)	
Male	104.1 (13.0)
Female	98.8 (12.8)
HbA_1c_ (%), mean (SD)	7.9 (0.8)
HbA_1c_ (%), n (%)	
<8.5	1173 (75.9)
≥8.5	372 (24.1)
Fasting plasma glucose (mg/dL), mean (SD)	149.9 (33.9)^a^
HOMA-IR (mU/L x mmol/L), mean (SD)	6.03 (5.31)^b^
HOMA-B (mU/mmol), mean (SD)	77.0 (79.0)^c^
Cardiovascular medications, n (%)	1174 (76.0)
Antihypertensive agents	933 (60.4)
Lipid lowering agents	805 (52.1)
Acetylsalicylic acid	498 (32.2)
Systolic blood pressure (mmHg), mean (SD)	133.5 (15.9)
Diastolic blood pressure (mmHg), mean (SD)	79.5 (9.4)
Blood pressure controlled (<130/80 mmHg), n (%)	
Yes	486 (31.5)
No	1059 (68.5)
Serum lipids (mmol/L), mean (SD)	
Total cholesterol^d^	4.49 (1.01)
HDL-cholesterol^e^	1.25 (0.31)
LDL-cholesterol^f^	2.42 (0.86)
Triglycerides^e^	1.86 (1.29)
Markers of renal function and damage	
eGFR (mL/min/1.73 m^2^) according to MDRD, mean (SD)	88.0 (17.3)
eGFR (mL/min/1.73 m^2^) according to MDRD, n (%)	
≥90 (normal renal function)	633 (41.0)
60 to <90 (mild renal impairment)	877 (56.8)
30 to <60 (moderate renal impairment)	35 (2.3)
Urine albumin/creatinine ratio (mg/g), mean (SD)	40.22 (135.59)
Urine albumin/creatinine ratio (mg/g), n (%)	
<30 (normal)	1221 (79.0)
30 to <300 (microalbuminuria)	289 (18.7)
≥300 (macroalbuminuria)	35 (2.3)

*Legend:**T2DM* type 2 diabetes mellitus, *HbA*_*1c*_ glycosylated hemoglobin, *HOMA-IR* homeostasis model assessment of insulin resistance, *HOMA-B* homeostasis model assessment of beta-cell function, *eGFR* estimated glomerular filtration rate, *MDRD* Modified Diet Renal Disease formula. ^a^n=1543; ^b^n=1441; ^c^n=1440; ^d^n=1518; ^e^n=1517; ^f^n=1516.

## Discussion

This head-to-head trial aims to establish comparative effectiveness between the SGLT2 inhibitor empagliflozin and the sulfonylurea glimepiride, used as second-line therapy in patients with T2DM in whom metformin and diet/exercise has failed, with regard to glycemic control, beta-cell function, diabetes-associated comorbidities such as obesity and hypertension, and safety, including macro- and renal microvascular complications, over 4 years.

This study is the largest head-to-head trial comparing an SGLT2 inhibitor with an SU to date [45,46]. As is typical of patients with T2DM, most of the patients in this study were overweight or obese and the majority had hypertension. The large number of patients enrolled in this study will enable important sub-group analyses to be performed, including analyses by the stratification factors baseline HbA_1c,_ eGFR, and region, but also analyses by baseline HOMA-IR, HOMA-B and BMI to characterize the efficacy of empagliflozin versus glimepiride in distinct subpopulations. Every effort is being made to keep patients randomized in the trial, for example, by allowing downtitration of SU to prevent recurrent hypoglycemia, by allowing patients who take rescue medication to stay in the trial, and by imposing very limited restrictions on concomitant medications. Every effort is being made to follow-up with patients who discontinue study drug.

Durability of efficacy and preservation of beta-cell function are important unmet medical needs in the treatment of patients with T2DM. This study will compare the effect of the insulin secretagogue glimepiride with empagliflozin, which has an insulin-independent mode of action, on the annualized slope of glycemic control (coefficient of durability) and biomarkers of insulin secretion over 4 years. Furthermore, the study design includes a 4-week follow-up period to assess, using a mixed MTT, whether empagliflozin truly delays or masks deterioration of beta-cell function during treatment through urinary glucose excretion.

Identification of chronic kidney disease and its progression is based on the assessment of renal function (eGFR) and markers such as albuminuria [47]. Recommendations for intensive glycemic control for prevention or delay of diabetic nephropathy are based almost exclusively on studies that have demonstrated an improvement in albuminuria [47]. In patients with T2DM and chronic kidney disease, glycemic control is recommended to be part of a multifactorial intervention strategy that includes blood pressure control [47]. Thus, empagliflozin, which lowers blood pressure and body weight as well as improving glycemic control, may offer an advantage over glimepiride in reducing the onset or deterioration of albuminuria as a surrogate marker of glomerular and tubular damage. A limitation of this study is that as the incidence of doubling of serum creatinine, end-stage renal disease or death from renal disease is expected to be low in these patients with normal renal function or mild renal impairment at baseline, this study is not powered to detect differences in hard renal outcome events.

Reduction of macrovascular complications is an important goal in the management of patients with T2DM. While this study is not powered to detect a difference in CV outcomes - assuming a yearly rate of 4-MACE (major adverse cardiac events) (CV death, non-fatal myocardial infarction, non-fatal stroke, hospitalization for unstable angina) of 1% in this low-risk population, one might expect approximately 60 adjudicated 4-MACE in a 4-year trial - exploratory comparative effectiveness data could support treatment decisions until hard evidence emerges from dedicated CV outcome trials.

